## Abstract

(1) Background: Patients with diabetes mellitus (DM) are at increased risk for heart failure (HF). Accurate data regarding the prevalence of HF stages among diabetics in Greece are scarce. (2) Aim: The present study will examine the prevalence and evolution of HF stages among patients with type II DM (T2DM) diagnosed in the past 10 years, with no previous history of HF and at high CV risk, in Greece, as well as will explore the potential determinants of the development of symptomatic HF in these patients. (3) Methods: Through a non-interventional, epidemiological, single-country, multi-center, prospective cohort study design, a sample of 300 consecutive patients will be enrolled in 11 cardiology departments that are HF centers of excellence. Patients will be either self-referred or referred by primary or secondary care physicians and will be followed for up to 24 months. Demographic, clinical, echocardiography, electrocardiography, cardiac biomarkers (troponin, NT-proBNP) and health-related quality of life questionnaire data will be recorded as well as clinical events, including mortality, HF hospitalizations and HF-related healthcare resource utilization. The primary outcomes are the proportion of patients diagnosed with symptomatic HF (ACC/AHA Stage C) at enrolment in the overall study population and the proportions of patients with HF stages A, B and C, as well as by NYHA functional classification in the overall study population. (4) Conclusions: The HF-LanDMark study is the first epidemiological study that will assess the prevalence of HF among T2DM patients in Greece that could potentially enhance prompt therapeutic interventions shown to delay the development of HF in the T2DM patient population (HF-LanDMark, Clinical Trials.gov number, NCT04482283).

## 1. Introduction

Diabetes mellitus (DM) is a major public health problem, with over 400 million adults diagnosed worldwide. The prevalence of the disease is increasing, and, by 2040, the International Diabetes Federation (IDF) estimates that approximately 700 million adults will be diagnosed with DM [1]. Clinical and epidemiological data indicate that patients with DM are at high risk for adverse outcomes, such as myocardial infarction and other atherosclerosis-related cardiovascular (CV) events [2], as well as renal failure. Heart failure (HF) is a major contributor to cardiovascular (CV) morbidity and mortality in DM, with prevalence in type II DM (T2DM) up to 28% [3]. Risk factors for HF in DM include established CV disease, the presence of CV risk factors and chronic kidney disease [4,5]. Importantly, patients with both HF and DM have a higher risk of CV death or HF hospitalization than patients with either one of the diseases alone [6].

As per the ACC/AHA HF classification, patients with DM have, at least, stage A HF, i.e., are at risk for developing clinical HF. The distribution of DM patients in HF stages A/B/C was 48%, 36% and 16% in a study of patients of age ≥ 60 years with previously unrecognized HF [7]. Over a quarter of T2DM patients aged ≥60 years may have unrecognized clinical HF [8]. The risk of progression to symptomatic HF (stage C) from asymptomatic left ventricular diastolic dysfunction or systolic dysfunction (Stage B) is 8- and 2-fold higher than the respective risk of stage A [9]. The global longitudinal strain may independently predict incident HF among stage B patients [10,11]. Cardiac biomarkers, including high-sensitivity cardiac troponin T (hs-cTnT) and amino-terminal pro-B-type natriuretic peptide (NT-proBNP), can enhance the recognition of HF among at-risk individuals, including T2DM, when combined with traditional risk scores [12]. Recently, a biomarker risk score that included high-sensitivity troponin T, NT-proBNP, high-sensitivity C-reactive protein and left ventricular hypertrophy on electrocardiogram was shown to stratify HF risk in patients with dysglycemia (diabetes and pre-diabetes) and inform the allocation of HF prevention therapies in these patients [13].

The prevalence of DM among Greek adults based on data from the electronic prescription database has been previously reported as 8.2% [14]. However, accurate epidemiological data regarding the prevalence of HF stages among diabetics in Greece are scarce. The HF prevalence and evolution of HF in DM II patients at high risk (HF-LanDMark) epidemiological study aims to generate novel real-world data on the prevalence and evolution of HF stages in Greece and to explore potential determinants of the development of symptomatic HF, among patients with T2DM diagnosed in the past 10 years who are at high CV risk. Furthermore, it will attempt to measure the burden of HF- and CV-related healthcare resource utilization (HCRU) based on the HF stage and to capture the impact of symptomatic HF on patient-perceived health status.

## 2. Methods

### 2.1. Study Design

HF-LanDMark is an observational, non-interventional, epidemiological, single-country, multicenter, prospective cohort study that will examine the prevalence of previously undiagnosed symptomatic HF and the distribution of HF stages A/B/C in T2DM patients diagnosed within 10 years from enrolment, with no previous history of HF, who have high or very high CV risk (as outlined in 2019 European Guidelines on diabetes, pre-diabetes and CV diseases) [15].

This study received approval from the ethics committee of all participating departments (Ethics approval number 371/7-7-2020), and all patients will sign informed consent before enrolment.

### 2.2. Patient Population

Approximately 300 consecutive eligible patients, managed in real-life clinical settings in Greece, will be recruited in 11 Cardiology Departments that are HF centers of excellence. Patients will be either self-referred or referred by primary or secondary care physicians (endocrinologists, diabetologists, internists, other) to Cardiology Departments. Patients aged between 40 and 80 years with T2DM diagnosed within 10 years prior to enrolment who are at high or very high CV risk are eligible to be included in the study. High or very high CV risk is defined according to 2019 guidelines on diabetes, pre-diabetes and CV diseases from the European Society of Cardiology. Briefly, very high CV risk is defined as having either established CVD (ischemic heart disease (IHD), cerebrovascular disease (CeDV), peripheral arterial disease (PAD)) or other target organ damage (proteinuria, left ventricular hypertrophy (LVH) or retinopathy), or at least three major risk factors (age, hypertension, dyslipidemia, smoking and obesity (body mass index, BMI ≥ 30 kg/m^2^). High CV risk is defined as age ≥ 50 years and presence of at least one additional major risk factor. Recruitment will last up to 27 months. Each participating patient will be followed for up to 24 months or until death, withdrawal of consent or physician’s decision for patient withdrawal, whichever occurs earlier. Main exclusion criteria are diagnosis of T1DM, prior history of HF or treatment with SGLT2 inhibitor at the time of study enrolment because of the effect of this drug class to reduce new-onset HF in patients with T2DM. Detailed inclusion and exclusion criteria are listed in the Supplementary Materials.

### 2.3. Study Methods

The study design and flow chart are presented in Figure 1. Patient follow-up visit frequency will be determined by the participating hospital-based investigators. However, study-related data will be collected at enrolment and at 6-, 12-, 18- and 24-month timepoints post-enrolment. Data collection at enrolment, and at 6 and 24 months post-enrolment will be performed in the context of on-site routine clinical visits at the hospital sites, whereas data collection at 12 and 18 months will be performed through telephone contacts.

### 2.4. Study Variables

Data collection will be prospectively carried out by means of a web-based data capture system. The following variables will be recorded upon study enrolment and at follow-up timepoints (Figure 1): sociodemographic data; anthropometric data; lifestyle habits (smoking, alcohol consumption, physical activity); vital signs; clinical history, including information related to T2DM, CVD, CV risk factors and other medical history; information regarding treatment for T2DM, CVD, CV risk factors and exposure to drugs that may cause or exacerbate HF; clinical data (HF symptoms/signs, NYHA functional status, stage and phenotype of HF); functional limitation/quality of life via Kansas City Cardiomyopathy Questionnaire-12; routine hematology, biochemitry and urine testing; 12-lead electrocardiography; cardiac function via echocardiography; serum cardiac biomarkers (NTproBNP, troponin); and CV events of interest after study enrolment (mortality; hospitalizations for HF and for other CV-related reasons; HF-and CV-related HCRU other than hospitalizations).

### 2.5. Study Objectives

The primary outcomes of the study are as follows: the proportion of patients diagnosed with symptomatic HF (Stage C) at enrolment in the overall study population, and the proportions of patients with HF stages A, B and C at enrolment, in the overall study population and based on NYHA functional classification. Select secondary outcomes include the following: the proportion of patients having progressed to higher HF stage at 2 years post-enrolment in the overall study population and in the subpopulations with HF stages A, B and C at enrolment; person-time incidence rate of symptomatic HF (stages C or D) defined as number of patients diagnosed with symptomatic HF per patient-years of observation since enrolment, in the study subpopulation with preclinical HF (stages A and B) at enrolment; proportions of patients with HF with reduced (HFrEF), mildly reduced (HFmrEF) and preserved left ventricular ejection fraction (HFpEF), overall and in the subpopulations with HF stages B and C at enrolment; change in the KCCQ-12 overall summary score and domain scores from enrolment to 6 and 24 months post-enrolment in the study subpopulation diagnosed with symptomatic HF (stage C) at enrolment; and person-time incidence rate of inpatient hospitalizations, emergency room attendances, admissions to an outpatient facility, visits at office-based physicians, home visits by physicians as well as medical procedures/interventions/diagnostic testing utilization for HF- and CV-related causes, in the overall study population and in the subpopulations with HF stages A, B and C at enrolment. A complete list of the secondary and exploratory outcomes of the study is presented in the Supplementary Materials.

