### 2.6. Statistical Analysis

This study does not aim to confirm or reject any pre-defined hypotheses; therefore, statistical analysis will mainly be of descriptive and exploratory nature. Inferential statistics will be used for the estimation of the confidence intervals (CIs) of the primary and secondary outcomes (as applicable) as well as in the context of the exploratory outcome analyses. Continuous variables will be summarized using descriptive statistical measures (number of patients with available observations (n_pt_), number of missing observations (n_miss_), mean, standard deviation (SD), median, 25th and 75th percentiles, minimum (min) and maximum (max)), and categorical variables will be displayed using frequency tables (n_pt_, %). The normality of distribution of continuous variables will be examined using the Shapiro–Wilk test. Differences from baseline will be assessed using repeated measures analysis of variance (ANOVA). Concerning binomial proportions, the 95% CIs will be derived from Wald confidence limits for binomial proportions, while for incidence rates, the 95% Poisson CIs will be estimated. Time-to-event analysis will be conducted using the Kaplan–Meier method.

The impact of patients’ characteristics on variables of interest will be evaluated using binary or multinomial logistic regression models for nominal outcome variables. Cox proportional hazard regression models will be applied in order to examine the association of selected factors of interest with the time-to-event outcome variables. Multivariable regression models may be fitted, providing that the number of events/patients in each model is sufficient to allow for meaningful inferences. Missing covariates will be addressed within the appropriate imputation method.

All analyses will be performed in the set of all eligible enrolled patients and in the subpopulations of interest. A comprehensive and detailed description of the statistical methodology for the purposes of the analysis along with imputation methods for missing dates, missing covariates and censoring rules for Kaplan–Meier estimations will be provided in the statistical analysis plan (SAP). All statistical tests will be two-sided, and *p* values will be reported.

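### The symptomatic-HF incidence rate does not end person-time at diagnosis, and onset first found at the 24-month visit is known only to within an 18-month interval

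*Protocol article*

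**What the plan says.** Section 2.5 of the protocol article lists, as a secondary outcome, a person-time incidence rate of symptomatic HF (stage C or D), "defined as number of patients diagnosed with symptomatic HF per patient-years of observation since enrolment". The population is restricted: "in the study subpopulation with preclinical HF (stages A and B) at enrolment". The clock's start is given; its stop is not. Section 2.2 ends follow-up at 24 months or at earlier death or withdrawal. A diagnosis of symptomatic HF is not among the reasons for ending it.

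On timing of assessments, section 2.3 states: "Data collection at enrolment, and at 6 and 24 months post-enrolment will be performed in the context of on-site routine clinical visits", "whereas data collection at 12 and 18 months will be performed through telephone contacts". The same section also says: "Patient follow-up visit frequency will be determined by the participating hospital-based investigators". Section 2.4 lists "clinical data (HF symptoms/signs, NYHA functional status, stage and phenotype of HF" among the variables recorded, together with echocardiography, cardiac biomarkers and HF hospitalizations. Which item belongs to which timepoint is in Figure 1, which is not shown.

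On methods, section 2.6 gives Poisson intervals for rates and states: "Time-to-event analysis will be conducted using the Kaplan–Meier method". Cox regression is to be used "to examine the association of selected factors of interest with the time-to-event outcome variables". No interval-censored method is named. Imputation of missing dates and the Kaplan-Meier censoring rules are left to the SAP.

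**The concern.** There are two separate issues.

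**Denominator.** The numerator counts patients, that is, first diagnoses. A patient who already has stage C or D can no longer contribute a first diagnosis, so later time is not time at risk. Leaving it in the denominator can only lower the rate.

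**Dating of onset.** Staging draws on signs, echocardiography and biomarkers, which a telephone call does not supply. A patient in stage A/B at 6 months and in stage C at 24 months had onset somewhere in between. Analysing the detection date as the onset date moves such events to the end of the interval. That distorts a time-to-event curve between visits, and it lengthens the person-time even when time is stopped at diagnosis.

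Two-year incidence is highlighted in the article's Conclusions, and determinants of symptomatic HF are a stated aim in the Introduction. Both analyses could be affected.

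**Working it through.** The article gives no incidence rate, event count or precision target, so there is no figure of the plan's own to reproduce. The check uses closed-form expectations.

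**Inputs from the article**
- Follow-up of 2 years (section 2.2).
- On-site data collection at 0.5 and 2 years (section 2.3).
- About 300 patients (section 2.2).
- For scale only, the A/B/C split of 48/36/16% that the Introduction cites from another study: 300 × (0.48 + 0.36) = 252 at risk.

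**Assumptions**
- Constant onset rate λ, from 0.02 to 0.20 per patient-year.
- No dropout, except where stated.
- For the detection-delay figures, no diagnosis outside the 6- and 24-month visits.

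**Formulas**, with S(t) = exp(−λt)
- Two-year risk: 1 − S(2).
- True time at risk per patient: (1 − S(2))/λ.
- All observation time: 2.
- Time to the detecting visit: 0.5 + 1.5·S(0.5).
- Midpoint dating: 0.25·(1 − S(0.5)) + 1.25·(S(0.5) − S(2)) + 2·S(2).

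**Numbers for λ = 0.10**
- Two-year risk = 1 − exp(−0.2) = 0.1813.
- True time at risk: 0.1813/0.10 = 1.813, rate 0.1000.
- All observation: 0.1813/2 = 0.0906.
- Time to detecting visit: 0.5 + 1.5 × 0.9512 = 1.927; 0.1813/1.927 = 0.0941.
- Midpoint: 0.25 × 0.0488 + 1.25 × 0.1325 + 2 × 0.8187 = 1.815; 0.1813/1.815 = 0.0999.

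| True rate | All observation time | Time to detecting visit | Midpoint dating |
|---|---|---|---|
| 0.02 | 0.0196 (−2.0%) | 0.0198 (−1.2%) | 0.0200 (0.0%) |
| 0.05 | 0.0476 (−4.8%) | 0.0485 (−3.0%) | 0.0500 (0.0%) |
| 0.10 | 0.0906 (−9.4%) | 0.0941 (−5.9%) | 0.0999 (−0.1%) |
| 0.20 | 0.1648 (−17.6%) | 0.1775 (−11.2%) | 0.1989 (−0.6%) |

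The first bias does not depend on when onset is detected, as long as it is detected by 24 months. The second is the extreme case; if onsets were dated on a 6-month grid, it would shrink to −1.2% at λ = 0.05 and −2.5% at λ = 0.10.

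**Curve between visits, no interim diagnoses**
- At 12 months the estimate is still 1 − S(0.5), against a true 1 − S(1): 4.9% against 9.5% at λ = 0.10, and 2.5% against 4.9% at λ = 0.05.
- At 18 months: the same 4.9% against 13.9%, and 2.5% against 7.2%.
- At 24 months there is no difference.
- Share of two-year onsets in the 6-24 month gap: (S(0.5) − S(2))/(1 − S(2)) = 0.1325/0.1813 = 73% at λ = 0.10 (71-75% over the range).
- Mean delay to detection: about 7.5 months.

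**Dropout (simulation, 2,000,000 patients)**. With an assumed loss or death hazard of 0.05 or 0.10 per year, about 3% or 6% of onsets are never detected. At λ = 0.10 the rate over all observation time falls to 0.088 or 0.086.

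**Scale against sampling error**. At λ = 0.10, 252 × 0.1813 = 45.7 events, and the Poisson 95% half-width is about 1.96/√45.7 = 29%. At λ = 0.05 there are 24.0 events and the half-width is 40%.

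**The case against.** A reader might infer that symptomatic HF can be diagnosed in person only at 6 and 24 months, so that the curve must stay flat and then jump at 24 months. The article does not support that. Section 2.3 leaves visit frequency to the investigators, and section 2.4 records HF hospitalizations and other HF-related resource use. A patient who becomes symptomatic at month 10 can be diagnosed and dated. The halved 12-month estimate is therefore a limiting case.

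A reader might also infer that the plan commits to treating onset as exactly observed. Section 2.6 names Kaplan-Meier and Cox in general terms, does not name symptomatic HF as their outcome, and leaves missing-date imputation and censoring rules to an SAP that is not shown. Nor does the article show that hazard ratios will be distorted by sicker patients being seen more often. This is possible under investigator-set visits, but nothing in the article allows it to be sized.

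On the denominator, it can be said that a person-time incidence rate conventionally stops at the event and that the wording is merely condensed. That is fair as to intent. But the outcome definition is fixed in section 2.5, and section 2.2 lets observation run on past diagnosis, so the literal reading is the wrong one.

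Finally, the rate bias is smaller than the sampling error, the listed two-year progression proportion needs no onset date, and the study is mainly descriptive. All of this stands and limits the severity. It does not remove a one-directional error that a clause would prevent. Rules for right-censoring or for missing dates do not by themselves deal with an onset whose detection date is known but whose true date is not.

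**Conclusion.** The point holds in limited form. Read literally with section 2.2, the rate definition in section 2.5 keeps time after diagnosis in the denominator and understates the rate by about 5-9% at 0.05-0.10 per patient-year (2-18% over 0.02-0.20). Separately, the 18-month gap between scheduled on-site assessments means that onset first found at 24 months is interval-censored, and none of the named methods handles that. If Kaplan-Meier or Cox is applied to symptomatic HF on the detection date, events are placed late. The 12-month estimate falls to about half the truth if there are no interim diagnoses, and by less if there are. Without dropout the 24-month value is unaffected.

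All onset and loss rates are assumptions, since the article gives none. Severity is moderate: the point touches a secondary outcome and the exploratory determinants analysis. Both primary outcomes are measured at enrolment and are untouched.

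**What to change.** 1. **Denominator.** Define it as person-time at risk: from enrolment to the first of stage C/D diagnosis, death, withdrawal or last assessment of HF status.
2. **Onset found at a scheduled visit.** Stopping at diagnosis alone leaves the 3-6% delay bias when onset is found only at scheduled visits. Treat such onset as interval-censored between the last stage A/B assessment and the first stage C/D assessment: an interval-censored model for determinants, and midpoint dating for the rate (residual bias 0.1% or less at 0.05-0.10 per patient-year under the assumptions above).
3. **Interim diagnoses.** Use the actual date for diagnoses made at unscheduled visits or HF hospitalizations.
4. **Alternative to 2.** Label the outcome time to diagnosis and base cumulative incidence statements on 6 and 24 months only.

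The cost is a change of wording in the outcome definition and the SAP, somewhat more complex models, and wider intervals; the alternative gives up 12- and 18-month incidence statements. No new data collection should be needed, provided that the web-based capture system holds the dates of assessments and diagnoses, which the article does not state.

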### 2.6. Statistical Analysis

This study does not aim to confirm or reject any pre-defined hypotheses; therefore, statistical analysis will mainly be of descriptive and exploratory nature. Inferential statistics will be used for the estimation of the confidence intervals (CIs) of the primary and secondary outcomes (as applicable) as well as in the context of the exploratory outcome analyses. Continuous variables will be summarized using descriptive statistical measures (number of patients with available observations (n_pt_), number of missing observations (n_miss_), mean, standard deviation (SD), median, 25th and 75th percentiles, minimum (min) and maximum (max)), and categorical variables will be displayed using frequency tables (n_pt_, %). The normality of distribution of continuous variables will be examined using the Shapiro–Wilk test. Differences from baseline will be assessed using repeated measures analysis of variance (ANOVA). Concerning binomial proportions, the 95% CIs will be derived from Wald confidence limits for binomial proportions, while for incidence rates, the 95% Poisson CIs will be estimated. Time-to-event analysis will be conducted using the Kaplan–Meier method.

The impact of patients’ characteristics on variables of interest will be evaluated using binary or multinomial logistic regression models for nominal outcome variables. Cox proportional hazard regression models will be applied in order to examine the association of selected factors of interest with the time-to-event outcome variables. Multivariable regression models may be fitted, providing that the number of events/patients in each model is sufficient to allow for meaningful inferences. Missing covariates will be addressed within the appropriate imputation method.

All analyses will be performed in the set of all eligible enrolled patients and in the subpopulations of interest. A comprehensive and detailed description of the statistical methodology for the purposes of the analysis along with imputation methods for missing dates, missing covariates and censoring rules for Kaplan–Meier estimations will be provided in the statistical analysis plan (SAP). All statistical tests will be two-sided, and *p* values will be reported.

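### Repeated measures ANOVA for KCCQ-12 change would, in its classical form, keep only stage C patients with all three assessments, and would overstate improvement if worsening patients leave

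*Protocol article*

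**What the plan says.** Section 2.6 (Statistical Analysis) names one method for change scores: "Differences from baseline will be assessed using repeated measures analysis of variance (ANOVA"). The sentence does not mention KCCQ-12. Section 2.5 (Study Objectives), however, lists as a secondary outcome "change in the KCCQ-12 overall summary score and domain scores from enrolment to 6 and 24 months post-enrolment", to be assessed "in the study subpopulation diagnosed with symptomatic HF (stage C) at enrolment". That is a difference from baseline on three occasions, so the sentence applies to it.

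Section 2.3 places the enrolment, 6-month and 24-month data collection at on-site visits. Section 2.2 allows follow-up to end early through death, withdrawal of consent or the physician's decision. On missing data, section 2.6 announces imputation for dates and covariates and censoring rules for Kaplan–Meier, with details left to the SAP. Missing outcome scores are not on that list. The same section says that continuous variables will be summarised with the number of patients observed and the number missing.

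**The concern.** Classical repeated measures ANOVA needs a score at every occasion for every patient. A patient who attends at enrolment and 6 months but not at 24 months contributes nothing, although two of the three scores exist. If those who leave had worsened by 6 months, removing them raises the estimated change at both later visits. Health status in symptomatic heart failure would then look better than it is. The objection is to the method that the article names, not to detail that the SAP may supply.

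**Working it through.** **No planned figure to reproduce.** The article gives no dropout rate, KCCQ-12 SD, within-patient correlation or expected stage C count. Everything numerical below is conditional on stated assumptions.

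**Number of patients.** Section 2.2 plans "Approximately 300 consecutive eligible patients, managed in real-life clinical settings in Greece". The introduction reports that "The distribution of DM patients in HF stages A/B/C was 48%, 36% and 16% in a study of patients of age ≥ 60 years", which would give 0.16 × 300 = 48. It also says "Over a quarter of T2DM patients aged ≥60 years may have unrecognized clinical HF", which would give more than 0.25 × 300 = 75. Both figures come from people aged 60 or over, whereas this study takes "Patients aged between 40 and 80 years with T2DM diagnosed within 10 years prior to enrolment". Assumed shares of 10% to 28% give 30 to 84 patients. The expected bias does not depend on this number; the precision does.

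**Who is kept.** With 48 patients and three visits, a standard repeated-measures ANOVA routine (AnovaRM in statsmodels) stops with an unbalanced-data error once ten patients lack the 24-month score. The incomplete patients have to be removed before it will run.

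**Bias of the completers' mean.** Assumptions:
- SD 20 at each visit.
- Correlations 0.6 (enrolment with 6 months), 0.5 (enrolment with 24 months) and 0.65 (6 with 24 months).
- Everyone seen at 6 months.
- Loss *d* at 24 months, with logit P(missing) = *a* − ln(OR) × *z*, where *z* is the standardised 6-month change and *a* is set to give *d*. This is missing at random (MAR), because it depends only on observed scores.

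Formulas:
- SD of the 6-month change = 20 × √(2 × (1 − 0.6)) = 17.9.
- Bias at 6 months = 17.9 × E(*z* | 24-month score present).
- Slope of 24-month change on 6-month change = (0.65 − 0.6 − 0.5 + 1) / (2 × (1 − 0.6)) = 0.55/0.8 = 0.6875.
- Bias at 24 months = 0.6875 × bias at 6 months.

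| OR per SD of worsening | Loss at 24 months | E(*z*, seen) | Bias at 6 months | Bias at 24 months |
|---|---|---|---|---|
| 1.00 (random) | any | 0 | 0 | 0 |
| 1.28 | 10% | 0.0245 | +0.44 | +0.30 |
| 1.28 | 25% | 0.0610 | +1.09 | +0.75 |
| 1.65 | 10% | 0.0489 | +0.88 | +0.60 |
| 1.65 | 25% | 0.1197 | +2.14 | +1.47 |
| 3.50 | 10% | 0.1078 | +1.93 | +1.33 |
| 3.50 | 25% | 0.2487 | +4.45 | +3.06 |

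For scale, the 95% half-width for a mean 6-month change in 48 complete patients is 2.01 × 17.9/√48 = 5.2 points.

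**What a likelihood model recovers.** A separate simulation used 48 patients, SD 20, all correlations 0.6, 5% random loss at 6 months, 20% loss at 24 months and 800 runs per scenario (Monte Carlo error about 3/√800 ≈ 0.1).
- MAR loss: completers were biased by +2.8 to +4.4 points at 6 months and +1.3 to +2.2 at 24 months. The likelihood estimate on all observed scores was biased by −0.03 to 0.00 and −0.18 to +0.09.
- Loss driven by the unseen 24-month change (missing not at random, MNAR): the 24-month bias fell only from +2.8 to +1.3.

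**Precision under random loss.** The completers' SE at 6 months grows by √(1/(1 − *d*)): √(1/0.80) = 1.12 and √(1/0.75) = 1.15, so it is 12-15% larger at 20-25% loss. In the simulation at 20% random loss, the 6-month SE was 3.02 for completers and 2.78 for the likelihood estimate. At 24 months it was 3.06 and 3.05, so there is nothing to gain there.

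**The case against.** **Descriptive summaries.** Section 2.6 calls the analysis mainly descriptive and summarises variables on the patients observed. A 6-month mean reported that way uses everyone seen at 6 months and escapes both the bias and the SE inflation when loss occurs only later. This stands: the 6-month figures above apply to the ANOVA result, not to such a table. It does not help at 24 months, where the observed mean carries the same selection. It would also leave the report with two differing 6-month results.

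**The SAP may handle it.** The article does not say that incomplete patients are deleted, and the SAP could implement the analysis as a mixed model. This is fair. A reader might infer that deletion is planned, but it is a property of the classical method named. The remedy is to name the model actually intended.

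**Size.** The upper figures need strong selection, and the article gives nothing from which to judge it. At an odds ratio of 1.28 the bias is about one point or less, and every 6-month bias in the table is below the 5.2-point half-width for 48 patients. This stands, and is why only a range can be given.

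**Sphericity.** A reader might add that visits 6 and then 18 months apart violate sphericity. Visit enters as a factor, so unequal spacing is not itself a violation. The correlations assumed above give a Greenhouse–Geisser epsilon of 0.96, which is negligible.

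**Lack of a comparator.** The introduction aims "to capture the impact of symptomatic HF on patient-perceived health status", and change within stage C alone has no comparison group. A reader might infer that a contrast with stages A and B is missing. Section 2.5 lists only selected secondary outcomes and refers to supplementary material for the rest, so this cannot be judged.

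**Conclusion.** The point holds as a poor choice of named method for one secondary outcome. Classical repeated measures ANOVA would discard observed scores and, if worsening patients leave, overstate improvement. Under the stated assumptions the bias ranges from zero (completely random loss) to about +4.4 points at 6 months and +3 at 24 months (25% MAR loss, odds ratio 3.5). The lower end under MAR is +0.4 and +0.3 points (10% loss, odds ratio 1.28). The direction follows from the mechanism; the size is not fixed by the documents.

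Three stronger readings are not supported. The study does not plan for 48 stage C patients; that number borrows an external share, and 30 to 84 is as plausible. Bias is not certain, since no dropout rate or mechanism is stated. Precision at 24 months would not improve with a better model. The primary prevalence outcomes are untouched.

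**What to change.** Replace the ANOVA sentence with a mixed model for repeated measures using all available observations: visit as a category, unstructured covariance and Kenward–Roger degrees of freedom. Report the number of deaths by visit alongside, and say what the KCCQ-12 estimate is meant to represent for patients who die, because the model does not settle that. Add a sensitivity analysis for MNAR loss, since the mixed model removes bias only under MAR. If a mixed model is already intended, saying so is enough for the main analysis.

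The cost is a wording change and slightly more analysis work. The data are the same and the software is standard.
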